##### Number of days with migraine and frequency of migraine attacks

Each patient with MwoA will record the number of days with migraine, frequency of migraine attacks, onset time, accompanying symptoms, duration, and methods used to relieve the headache in a headache diary (29, 30) during the trial.

##### Response rate

Response rate is defined as the proportion of patients with ≥50% reduction in the number of migraine days (31), which will be calculated at the end of treatment (week 8) and end of follow-up (week 20).

##### Average visual analog scale (VAS)

Average visual analog scale scores for pain will be used to assess changes in headache intensity from the baseline to the end of follow-up (32). Scores will be recorded every 4 weeks to evaluate the severity of headache for the previous 4 weeks.

##### Evaluation of emotional state and usage of ibuprofen

The emotional state of patients will be assessed using the *Zung* Self-rating Anxiety Scale (SAS) and Self-rating Depression Scale (SDS) at weeks 0, 4, 8, 12, 16, and 20. The use of ibuprofen during the trial will be recorded every 4 weeks.

#### Multimodal MRI data acquisition

MRI data will be acquired at week 0 with a 3.0T magnetic resonance scanner (GE Discovery 750; Milwaukee, WI, USA) with a 16-channel phase-array head coil at the MRI Center of the University of Electronic Science and Technology in China. Participants will be asked to lie in the supine position on the examination bed, stay awake, keep their head still, with eyes closed and ears plugged during the scan.

Three-dimensional T1-weighted (3D-T1) imaging will be performed to obtain high-resolution structural images for each participant with a voxel size of 1 mm^3^, using a spoiled gradient-recalled sequence (repetition time [TR], 6.008 ms; echo time [TE], 1.7 ms; field of view [FOV], 256 × 256 mm^2^; data matrix: 256 × 256). Resting-state blood oxygenation level-dependent (BOLD) signals will be obtained by gradient-recalled echo planar imaging (31 contiguous slices; slice thickness, 5 mm; TR, 2000 ms; TE, 30 ms; flip angle, 90°; FOV, 240 × 240 mm^2^; data matrix, 64 × 64; total volumes, 205).

To detect any white matter abnormalities, diffusion tensor imaging (DTI) will be performed with the following parameters: TR, 8500 ms; TE, 84 ms; data matrix, 128 × 128; FOV, 256 × 256 mm^2^; slice thickness, 2 mm; and 78 continuous axial slices with no gap. Two diffusion-weighted sequences will be acquired using gradient values b = 0 s/mm^2^ and 1,000 s/mm^2^ with diffusion-sensitizing gradients applied along with 64 non-linear directions.

### Data analysis

Collected data will be managed with printed case report forms (CRFs) and only outcome assessors will have access to these data. The research team will be responsible for data organization. Two data entry checks will be performed. The Ethics Committee of the First Affiliated Hospital of Chengdu University of Traditional Chinese Medicine will be supervising this study with a check-in every 3 months and will make the final decision on whether or when to terminate the trial.

#### Clinical data analysis

Clinical outcomes will be analyzed using SPSS v22.0 statistical software (IBM, Armonk, NY, USA). The level of statistical significance (two sided) will be set as 0.05 in all analyses. The per-protocol set was the primary population for efficacy analyses.

All continuous variables will be expressed as means with standard deviations. Categorical variables will be described as numbers and percentages. The Kolmogorov–Smirnov test will first be used to test the distribution of continuous variables. For normally distributed data, the paired-sample *t*-test will be used to evaluate differences within groups; when the data follow a skewed distribution, a non-parametric test will be used.

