## Abstract

**Introduction:**

Acupuncture is an effective and safe therapy for patients with migraine without aura (MwoA), but only 41–59% of patients show improvement with this treatment. Screening positive responders to acupuncture treatment for MwoA can ensure that healthcare resources can be appropriately targeted to specific patients who would most benefit. The objective of this study is to determine whether the structure and functional activity in certain brain regions can predict analgesia response in patients with MwoA who receive acupuncture treatment.

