## Introduction

Migraine is a common neurologic disorder characterized by recurrent attacks of disabling headaches that are often accompanied by nausea, vomiting, photophobia, and phonophobia (1). Migraine is the 7th leading cause of time spent disabled worldwide (2), with an estimated 1-year prevalence of 15% in the general population (3). At present, there are no satisfactory treatments for migraine (4–6). Acupuncture, an important component of traditional Chinese medicine, is recommended by the World Health Organization as an alternative and complementary therapy for migraine. Many randomized controlled trials and systematic reviews have demonstrated that acupuncture is safe and cost-effective with comparable efficacy to prophylactic drugs for migraine and can reduce headache intensity, frequency of migraine attacks, and number of migraine days (7–10).

However, only 41–59% of patients with migraine without aura (MwoA) experience symptom improvement with acupuncture treatment (9). This is associated not only with clinical but also with socioeconomic challenges. Therefore, identifying characteristics that can be used to predict migraineurs' response to acupuncture is important to improve the efficacy of the treatment and provide individualized therapy to patients who would most benefit.

Personalized medicine can be achieved by conducting clinical trials, assessing clinical outcomes, analyzing numerous characteristics, and identifying common and unique predictors of treatment outcomes. Previous studies have reported that patients' expectations, educational background, and treatment preferences influence the clinical efficacy of acupuncture for diseases characterized by pain (11–15). However, the questionnaires used in these studies were subjective and qualitative. Recently, with the development of neuroimaging techniques and artificial intelligence, magnetic resonance imaging (MRI) data have been used to predict the clinical efficacy of various interventions, including pharmacologic treatments (16), cognitive behavioral therapy (17), and placebo treatments (18), among others. These studies often provide more objective and reliable predictions than questionnaires.

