## Methods and analysis

### Study design

This non-randomized clinical trial will enroll 72 patients with MwoA and 72 with HCs. The study will last 24 weeks including a 4-week baseline period; for migraineurs, this will be followed by an 8-week treatment period and a 12-week follow-up period (Table 1). Structural and functional MRI scans will be performed at baseline. Clinical outcomes will be evaluated after treatment and during the follow-up. Figure 1 shows a flow diagram of the study. This protocol is reported in accordance with Consolidated Standards of Reporting Trials and Standards for Reporting Interventions in Clinical Trials of Acupuncture. The protocol was approved by the Institutional Review Board and Ethics Committee of the Hospital of Chengdu University of Traditional Chinese Medicine (approval no. 2020KL-058) and is registered with the Chinese Clinical Trial Registry (registration no. ChiCTR2100042915).

**Table 1 T1:** Standard protocol items: recommendations for interventional trials (SPIRIT) schedule of the trial.

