### Interventions

HCs will not receive any treatment during the trial. All patients with MwoA will receive the same acupuncture treatment procedure. *Baihui* (GV20), bilateral *Fengchi* (GB20), bilateral *Touwei* (ST8), bilateral *Shuaigu* (GB8), bilateral *Taiyang* (EX-HN5), bilateral *Hegu* (LI4), and bilateral *Taichong* (LR3) will be targeted by the acupuncture treatment (Figure 2).

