#### Classification and prediction using machine learning methods

Multivariate pattern analysis (34) will be carried out to classify migraineurs and HCs; this will include feature selection, model construction, and performance evaluation. Principal component analysis (35) will be performed and the searchlight algorithm (36) will be used to select features from multimodal parameters of brain regions, such as gray matter volume (GMV), ReHo, ALFF, fALFF, FA, and MD. The linear kernel support vector classification will be used to construct the classification model (37), which will be assessed by leave-one-out cross-validation (LOOCV). Clusters with a minimum accuracy of 70% will be identified as meaningful classifying features.

Patients with MwoA will be divided into the response and non-response groups (defined as ≥50% and <50% reduction, respectively, in the number of migraine days end of treatment compared with baseline). Support vector regression will be performed to discriminate between the response and non-response groups using the abovementioned classifying features of brain regions (ie, GMV, ReHo, ALFF, fALFF, FC, FA, and MD) (38). In addition to neuroimaging features, we may combine multidimensional features such as clinical data to build the model. After constructing the prediction model for patients with MwoA, LOOCV will be performed to evaluate the robustness of the model. A receiver operating characteristic (ROC) curve will be generated, and the area under the curve (AUC, 0–1) will be calculated to assess the power of the model. The performance of the SVR model will be quantified by calculating sensitivity and specificity based on the number of true positives and true negatives.

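### The per-protocol set is the primary efficacy population in a single-arm trial, so the response rate depends on adherence after treatment starts and probably overstates response among patients who begin acupuncture

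*Protocol article*

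**What the plan says.** The section Clinical data analysis states that "The per-protocol set was the primary population for efficacy analyses". The article does not define this set, names no full-analysis or all-treated set beside it, and gives no expected dropout and no rule for patients who stop treatment or lack outcome diaries.

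The design has a single treated group. Study design says "This non-randomized clinical trial will enroll 72 patients with MwoA and 72 with HCs", and Interventions says "All patients with MwoA will receive the same acupuncture treatment procedure". The healthy controls are untreated, and the Limitation section confirms that there is no sham arm.

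The section Response rate says "Response rate is defined as the proportion of patients with ≥50% reduction in the number of migraine days", calculated at week 8 and week 20. For the prediction model, the section on machine learning says "Patients with MwoA will be divided into the response and non-response groups", using the same 50% threshold at the end of treatment. That section does not name an analysis set.

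The abstract gives the purpose: "Screening positive responders to acupuncture treatment for MwoA can ensure that healthcare resources can be appropriately targeted".

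**The concern.** In its usual meaning, a per-protocol set is defined by what happens after treatment starts: sessions attended, data supplied, no major deviation. Here treatment is 12 sessions over 8 weeks with needles retained for 60 minutes, followed by 12 weeks of diary keeping. Patients who notice no benefit have the least reason to continue. If they leave the set more often than patients who improve, the remaining patients show a higher response rate than the group that began treatment.

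Two features of this trial make that matter. First, there is no comparator arm, so selective exclusion enters the reported proportion directly. The common reason for giving a per-protocol analysis weight, a non-inferiority comparison, does not apply. Second, the result is meant to inform selection of patients at baseline, when nobody knows who will complete. The rate that serves this purpose is the rate among all who start.

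The prediction model is affected only conditionally. If it too were restricted to the per-protocol set, it would be built on a selected range of patients (selection or spectrum bias). Its performance might then not carry over to those who would be screened.

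**Working it through.** The article gives no sample-size derivation, attrition rate or per-protocol definition, so there is no planned figure to reproduce. The calculation below is an illustration.

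**Inputs**
- N = 72 treated patients (Study design).
- p, the response rate in the per-protocol set: 50%, inside the range in the Introduction ("only 41–59% of patients with migraine without aura (MwoA) experience symptom improvement with acupuncture treatment"). That range is background, not a design assumption.
- d, the fraction excluded: assumed 5% to 30%.
- q, the response rate among excluded patients: assumed 0, half of p (25%), equal to p (50%), or 100%.

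**Formulas**
- Per-protocol size n = round(72 × (1 − d)); responders r = round(0.50 × n).
- Per-protocol rate = r/n.
- All-treated rate = (r + q × (72 − n))/72.
- The per-protocol rate therefore exceeds the all-treated rate by ((72 − n)/72) × (r/n − q). The sign of the bias depends on whether q is below or above the per-protocol rate; its size also depends on the fraction excluded.

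**Results**

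| Assumed d | Per-protocol rate | All treated, q = 0 | q = 25% | q = 50% | q = 100% |
|---|---|---|---|---|---|
| 5% | 34/68 = 50.0% | 34/72 = 47.2% | 48.6% | 50.0% | 52.8% |
| 10% | 32/65 = 49.2% | 32/72 = 44.4% | 46.9% | 49.3% | 54.2% |
| 15% | 30/61 = 49.2% | 30/72 = 41.7% | 45.5% | 49.3% | 56.9% |
| 20% | 29/58 = 50.0% | 29/72 = 40.3% | 45.1% | 50.0% | 59.7% |
| 30% | 25/50 = 50.0% | 25/72 = 34.7% | 42.4% | 50.0% | 65.3% |

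The 20% row in full, with 72 − 58 = 14 patients excluded:
- q = 0: 29/72 = 40.3%, a gap of 9.7 points.
- q = 25%: (29 + 3.5)/72 = 45.1%, a gap of 4.9 points.
- q = 50%: (29 + 7)/72 = 50.0%, no gap.
- q = 100%: (29 + 14)/72 = 59.7%, so the per-protocol rate is 9.7 points too low.

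At the ends of the quoted range, with d = 20% and q = 0, 24/58 = 41.4% becomes 24/72 = 33.3%, and 34/58 = 58.6% becomes 34/72 = 47.2%.

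For scale, the quoted range of 41% to 59% is 18 points wide. A 9.7-point gap is just over half of that, but it is reached only with about 20% excluded and no response at all among them.

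**The case against.** The strongest case on the other side has five parts.

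**The aim is prediction, not efficacy.** There is no between-treatment comparison and no threshold that the response rate must meet, so a shift in a descriptive proportion does not invalidate the main analysis. This stands as a limit on severity. The rate is still a reported outcome, and patient selection at baseline is the trial's stated purpose.

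**Per-protocol rules and further analysis sets may be in the full protocol or analysis plan.** That is possible, and their absence from the article is not the point. The choice of primary population is stated in the article, and a secondary set elsewhere would not change it.

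**The direction of bias is not established.** A reader might infer that the response rate is certainly inflated. The documents do not support that: they give neither attrition nor reasons for exclusion, and the table shows no bias or the opposite bias under other values of q. Overstatement is the most plausible direction, no more.

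**The prediction model may not use this set.** A reader might infer that the model is trained on completers, or that the responder labels are inflated. Neither follows. The per-protocol sentence belongs to the clinical analysis, and the machine-learning section names no set. Each label comes from that patient's own change in migraine days, so the analysis set cannot alter it; the set can alter only who is included and the mix of responders and non-responders. A different responder proportion alone would not change sensitivity or specificity; a different case mix would be needed. The article plans no predictive values.

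**Labelling every missing diary as non-response could harm the model.** A patient who leaves for unrelated reasons would be mislabelled, which adds noise to a model with at most 72 patients. This stands, and the fix treats the response rate and the model differently for that reason.

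**Conclusion.** The point holds for the response rate. Making the per-protocol set primary ties an absolute, single-arm proportion to behaviour after baseline, whereas the trial's purpose calls for the rate among all who start. The likely effect is overstatement. For a per-protocol rate near 50%, the gap is about 3 points at 5% exclusion and about 10 points at 20% if no excluded patient responds. It is roughly half that if they respond at half the rate, and nil if they respond equally. Both the exclusion fraction and the response among excluded patients are assumptions, as is the usual reading of per-protocol, which the article does not define.

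For the prediction model the conclusion is narrower. Its analysis set is unstated, and restricting it to the per-protocol set would risk selection bias. The documents do not show that this restriction is planned.

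**What to change.** - **Primary efficacy population:** all patients who receive at least one acupuncture session and have a baseline diary.
- **Response rate:** count a missing outcome diary as non-response at week 8 and week 20, with multiple imputation of migraine days as a sensitivity analysis.
- **Per-protocol set:** keep it as a sensitivity analysis only.
- **Prediction model:** state its population in the machine-learning section. Use all treated patients with an observed or imputed outcome, and label missing diaries as non-response only in a sensitivity analysis.

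The cost is a few sentences, some additional analysis, and a reported response rate that may be somewhat lower. No new data collection is needed. The Trial status section reports 15 patients recruited at the time of writing, so at that stage the change could have been made before most outcomes existed.

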#### MRI data preprocessing

BOLD functional MRI data will be preprocessed (i.e., slice timing, motion correction, spatial normalization, detrending, and bandwidth filtering) using MATLAB R2018a (Mathworks, Natick, MA, USA) and SPM12 (SPM12; Wellcome Department of Imaging Neuroscience, London, UK; http://www.fil.ion.ucl.ac.uk/spm/) software. After preprocessing, the amplitude of low-frequency fluctuation (ALFF), fractional ALFF (fALFF), regional homogeneity (ReHo), functional connectivity (FC), and other possible brain functional parameters will be analyzed. The 3D-T1 data will be analyzed by voxel-based morphometry using SPM12 and the CAT12 toolbox in MATLAB (33). DTI data will be preprocessed and analyzed using Functional Software Library v4.1.9 (http://fsl.fmrib.ox.ac.uk/fsl/fslwiki/TBSS/). Fractional anisotropy (FA) index and mean diffusivity (MD) maps will be obtained after head action correction, eddy current correction of DTI images, and tensor model fitting.

#### Classification and prediction using machine learning methods

Multivariate pattern analysis (34) will be carried out to classify migraineurs and HCs; this will include feature selection, model construction, and performance evaluation. Principal component analysis (35) will be performed and the searchlight algorithm (36) will be used to select features from multimodal parameters of brain regions, such as gray matter volume (GMV), ReHo, ALFF, fALFF, FA, and MD. The linear kernel support vector classification will be used to construct the classification model (37), which will be assessed by leave-one-out cross-validation (LOOCV). Clusters with a minimum accuracy of 70% will be identified as meaningful classifying features.

Patients with MwoA will be divided into the response and non-response groups (defined as ≥50% and <50% reduction, respectively, in the number of migraine days end of treatment compared with baseline). Support vector regression will be performed to discriminate between the response and non-response groups using the abovementioned classifying features of brain regions (ie, GMV, ReHo, ALFF, fALFF, FC, FA, and MD) (38). In addition to neuroimaging features, we may combine multidimensional features such as clinical data to build the model. After constructing the prediction model for patients with MwoA, LOOCV will be performed to evaluate the robustness of the model. A receiver operating characteristic (ROC) curve will be generated, and the area under the curve (AUC, 0–1) will be calculated to assess the power of the model. The performance of the SVR model will be quantified by calculating sensitivity and specificity based on the number of true positives and true negatives.

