**Methods and analysis:**

A total of 72 patients with MwoA and 72 healthy controls (HCs) will be enrolled in this study. Resting-state structural and functional magnetic resonance imaging (MRI) data will be collected from each participant at baseline. Patients with MwoA will undergo 12 sessions of acupuncture treatment for 8 weeks, twice per week in the first 4 weeks and once per week for the last 4 weeks. The follow-up will be 12 weeks. The number of days with migraine, frequency of migraine attacks, and average visual analog scale scores will be recorded in detail at weeks 0, 4, 8, 12, and 16 and at the end of follow-up (week 20). The positive response rate will be calculated as the proportion of patients with ≥50% reduction in the number of migraine days during follow-up compared with baseline. Machine learning methods will be applied to classify patients with MwoA and HCs and predict patients with response or non-response to acupuncture treatment based on multimodal MRI parameters, such as gray matter volume, regional homogeneity, amplitude of low-frequency fluctuation, fractional anisotropy, and mean diffusivity.

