**Discussion:**

This study aims to establish brain structural and functional characteristics that can identify patients with MwoA who will derive analgesia benefits from acupuncture treatment.

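### The 70% accuracy rule for naming brain regions has no controlled false-positive rate: it takes no account of how many searchlights and maps are tried or how many participants are analysed

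*Protocol article*

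**What the plan says.** The protocol article's section on classification and prediction by machine learning says that PCA will be performed and that "the searchlight algorithm (36) will be used to select features". The material searched is "features from multimodal parameters of brain regions, such as gray matter volume (GMV), ReHo, ALFF, fALFF, FA, and MD". A linear-kernel classifier separating patients from controls is then judged by LOOCV, and the decision rule follows: "Clusters with a minimum accuracy of 70% will be identified as meaningful classifying features". No null distribution, p-value, minimum cluster extent or confirmation step is attached to it. The clusters that pass become the stated imaging inputs of the model for response to acupuncture.

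The list of maps is open. The section on MRI data preprocessing adds functional connectivity and leaves room for further functional measures.

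Two statements elsewhere might be thought to supply the missing control. The section on clinical data analysis says: "The level of statistical significance (two sided) will be set as 0.05 in all analyses". That section deals with clinical outcomes, and the level is not linked to the 70% rule. The end of the Introduction describes a scheme with training, validation and test stages, but the machine learning section describes LOOCV only and does not say that selected clusters are confirmed in a test set.

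**The concern.** For one prespecified test in 144 people, 70% is far above chance. A searchlight does not make one test. It repeats the classification at every position of every map and keeps whatever passes. A cut-off that ignores the number of attempts allows a false-positive rate that grows with them, and a cut-off that ignores sample size becomes weaker as participants are lost. LOOCV accuracy under no effect also varies more than a binomial proportion, because the held-out predictions share nearly all their training data.

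This is a separate matter from reusing participants to evaluate the final model. Even with an untouched test set for that model, the list of regions would still be produced by an uncalibrated rule. At stake are the meaning of that list and the quality of what is handed to the response model.

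**Working it through.** **Inputs from the article.** Sample: "A total of 72 patients with MwoA and 72 healthy controls (HCs) will be enrolled in this study", so n = 144 and chance is 50%. Threshold: 0.70 × 144 = 100.8, so at least 101 correct. Maps: six are named.

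**Assumed, not in the article.** Number of positions M: 540 (90 regions × 6 maps); 50,000 or 64,000 for one whole-brain map; 300,000 for six maps. Searchlight of 33 voxels (radius 2 voxels); smoothing FWHM 0 to 3 voxels.

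**Step 1: the plan's own figure.** The 70% comes without a derivation or error rate, so there is nothing to reproduce. The natural benchmark is binomial: P(X ≥ 101 | 144, 0.5) = 7.4 × 10⁻⁷ per position, and 1 − (1 − p)^M over M independent positions.

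| Analysable n | Correct needed | p per position | M = 50,000 | M = 300,000 |
|---|---|---|---|---|
| 144 | 101 | 7.4 × 10⁻⁷ | 3.7% | 20% |
| 120 | 84 | 6.9 × 10⁻⁶ | 29% | 88% |

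On this model the 5% family-wise cut-off with 144 people is 99/144 (68.8%) for M = 10,000, 101/144 (70.1%) for 50,000 and 103/144 (71.5%) for 300,000. So 70% happens to suit one whole-brain map at full enrolment. With 120 people, p is about nine times larger at the same 70%.

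**Step 2: LOOCV null, raw voxels.** Pure-noise volumes, 72 versus 72, with closed-form LOOCV of a linear least-squares classifier. The SD of accuracy was about 0.054, against √(0.25/144) = 0.042 for a binomial proportion. The share of 13,824-position volumes with at least one position at 70% or more, scaled by 1 − (1 − q)^(M/13,824):

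| Smoothing (FWHM, voxels) | q | M = 50,000 | M = 300,000 |
|---|---|---|---|
| 0 | 0.402 | 84% | >99.9% |
| 2 | 0.312 | 74% | 99.97% |
| 3 | 0.181 | 51% | 98.7% |

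A separate simulation of 8,000-position maps gave q = 0.158 (FWHM 2) and 0.104 (FWHM 2.67). Scaled to 64,000 positions, 1 − (1 − q)^8 = 75% and 59%.

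**Step 3: PCA and cluster extent.** A third simulation (FWHM 2, 282 small volumes, about 774,000 positions) compared raw voxels with PCA.
- Raw voxels: 18 volumes with a hit. Expected number at 64,000 positions: 18 × 64,000/774,000 = 1.49; 1 − exp(−1.49) = 77%.
- 10 or 5 components: 2 volumes each. 2 × 64,000/774,000 = 0.165; 1 − exp(−0.165) = 15% per map. Over six independent maps: 1 − 0.85⁶ = 62%.
- Two or more adjacent positions, raw voxels: about 15% per map.

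The PCA figure rests on two events. The exact 95% Poisson interval, 0.24 to 7.22 events, corresponds to 2% to 45% per map. A smaller run of 108,000 positions gave 4 hits with raw voxels, 4 with 10 components and 1 with 5, so the benefit of mild reduction is uncertain. That run had no two adjacent positions both passing.

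**Step 4: regional search.** With the per-position rate of 3.7 × 10⁻⁵ from the unsmoothed volumes, 540 × 3.7 × 10⁻⁵ = 0.020, or about 2%. The binomial rate gives 540 × 7.4 × 10⁻⁷ = 0.0004.

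**The case against.** The strongest defence is that 70% is not a lax threshold: on the binomial benchmark it is close to a corrected cut-off for one whole-brain map. The rule also names clusters, while most false hits in the simulations were one or two adjacent positions. The article specifies PCA, which can lower the rate, and speaks of brain regions, so a modest regional search cannot be excluded. Patient-control classification serves partly as a feature screen, and a screen need not control family-wise error. Finally, a condensed article may leave searchlight settings and permutation testing to the full protocol.

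Much of this stands, and it limits what can be claimed. A reader might infer that the rule is likely to name regions when the groups do not differ. The documents do not support that: it holds for a voxelwise search on raw voxels, but not for a small regional search, and it is not shown for a search with strong PCA reduction in a single map. A reader might also infer that noise regions would produce a false response predictor. They would not by this route: the screen uses diagnosis labels and the response model uses responder labels, so regions picked by chance on diagnosis carry no responder information. They dilute the model. Nor should the abstract's closing statement of aim be cited as making migraine-versus-control features a main product, since it concerns patients who benefit from acupuncture.

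The defence does not repair the rule itself. The unstated settings are no fault in an article, but the rule is printed as definite, calls what passes meaningful rather than candidate, and stays at 70% whatever those settings are. The agreement with the binomial cut-off holds only for one map, full enrolment and independent predictions.

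**Conclusion.** The concern holds in this form: the 70% rule has no controlled false-positive rate, because its cut-off does not respond to the number of searchlights, the number of maps or the analysable sample size. The chance of at least one falsely named region runs from about 2% or less to near certainty, depending on choices outside the article, so a reader of the results could not tell what a positive list means. The list alone would not be evidence of a patient-control difference.

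The size rests on the assumed grid, searchlight radius and smoothing, on scaling from sub-volumes treated as independent, and on a least-squares classifier in place of the planned one. Small checks with a true linear SVC gave an SD of 0.057 to 0.072, at least as wide, but they were too few to show the tail at 70%, and a wider SD alone does not settle that tail. Near certainty over six maps requires independence. ALFF, fALFF and ReHo share one scan, and FA and MD one tensor, so the true figure for a raw-voxel search lies between the single-map value and that limit.

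This should be corrected before the imaging analysis, but it does not undermine the trial's design.

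**What to change.** Keep 70% as a minimum effect size and add a threshold calibrated to the search. Permute the patient/control labels, for example 1,000 times. In each permutation rerun PCA, searchlight and LOOCV across every map analysed, and record the maximum accuracy, or the maximum size of a cluster above 70%. Fix in advance which of the two is used. Call a cluster meaningful only if it passes 70% and exceeds the 95th percentile of that maximum, and report its corrected p-value. The list of maps should be closed before the analysis, so that the permutations cover the same search as the real data.

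This threshold adapts to the number of positions, the correlation between maps, the PCA dimension and the final sample size, and needs no assumption about any of them. It requires a change of wording and computing time, but no new data or participants. The article reports 15 patients recruited at the time of writing. The downside is that fewer clusters, possibly none, may be declared meaningful. The plan should therefore also say what enters the response model if none is.
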